# A community health worker-led multimedia intervention to increase cervical cancer screening uptake among South Asian women: study protocol for a cluster randomized wait-list controlled trial

**DOI:** 10.1186/s13063-019-3378-4

**Published:** 2019-05-14

**Keywords:** Cervical cancer, Community health worker, Screening, Multimedia

## Abstract

**Background:**

Marked ethnic disparities on cervical cancer screening have been observed among South Asian women. Multiple barriers, such as language difficulties, poor access to screening services, values, and beliefs, were identified. Multimedia interventions led by community health workers (CHWs) would likely reduce screening disparities and increase cervical screening uptake among South Asian women. This study aims to assess the effects of a CHW-led multimedia intervention on the uptake of cervical cancer screening among South Asian women.

**Methods:**

This study is a cluster randomized wait-list controlled trial. A total of 408 South Asian women from Pakistan, India or Nepal will be recruited from six ethnic minority associations. Each association will be randomized to one of the two arms: an intervention arm (*n* = 3) that will undergo immediate treatment (CHW-led multimedia intervention) or a wait-list control arm (*n* = 3) that will receive delayed treatment. Each recruited CHW will be allocated to either arm according to the association she is affiliated with. The intervention arm will receive a CHW-led intervention comprising two components: multimedia education, and monthly telephone follow-up and navigation assistance. Participants in the control arm (*n* = 3) will be offered the CHW-led intervention after those in the intervention arm have completed the intervention. The primary outcome measure is the uptake of cervical cancer screening. Secondary outcomes include readiness to undergo screening and beliefs regarding cervical cancer screening. Outcomes assessments will be performed at baseline, immediately after, and 3 months after completion of the intervention.

**Discussion:**

The results of this study will potentially provide significant practical implications for addressing the needs and increasing the uptake of cervical cancer screening among South Asian women.

**Trial registration:**

Chinese Clinical Trial Registry, ChiCTR1800017227. Registered on 18 July 2018.

**Electronic supplementary material:**

The online version of this article (10.1186/s13063-019-3378-4) contains supplementary material, which is available to authorized users.

## Background

Cervical cancer, one of the most common cancers that affect women in Hong Kong, poses a considerable healthcare burden [1]. In 2015, 500 new cases of cervical cancer were diagnosed with a crude incidence rate of 12.7 per 100,000 among the female population [1]. A total of 151 women died from this cancer in Hong Kong in 2016 [1]. Cancer screening should be conducted to detect premalignant lesions and ensure that proper management is implemented early to prevent development, to reduce the burden of cervical cancer [2]. Early detection through cancer screening also enables the availability of several treatment options, thereby improving survival rates and reducing healthcare costs [2]. In Hong Kong, women aged 25–64 years who have sexual experience are recommended to undergo a Papanicolaou test (Pap test) once every 3 years after two consecutive annual Pap tests with normal results. Furthermore, women aged 65 years or older who never have a cervical smear should undergo a Pap test [2].

As the largest (14%) and one of the fastest growing ethnic minority groups in Hong Kong [3], South Asians from India, Nepal, and Pakistan represent an important target for health intervention. Studies on the rate of cervical cancer among South Asians living in Hong Kong are currently lacking. However, studies in western countries have consistently demonstrated that the incidence of cervical cancer among South Asian women is comparable to or even higher than that among the general population in these countries [4, 5]. Marked ethnic disparities in cervical cancer screening have also been observed [6, 7].

A previous study demonstrated that more than half of South Asian women aged 40 years or older in Hong Kong never have a Pap test [7]. Their screening rate is also significantly lower than that of the local general population [7]. Factors that contribute to their low screening uptake rate include health illiteracy, lack of knowledge about cervical cancer and the importance of its early detection, misconceptions about cancer and screening, poor access to screening services, and language barriers [6, 8, 9]. Strategies to increase the rate of screening uptake among this underprivileged group should be developed to reduce the morbidity and mortality contributed by screening disparities.

Various interventions have been demonstrated to enhance knowledge of cervical cancer and promote screening intentions and uptake among ethnic minority women. However, several systematic reviews and meta-analyses have suggested that effective interventions share a number of common characteristics. These include: being theory based; being culturally tailored; being composed of multiple intervention strategies; and being delivered in a community setting with assistance in scheduling/attendance in screenings [10–12]. A recent theory-based and culturally tailored multimedia educational intervention to promote cervical cancer screening among South Asians using a one-group pretest and posttest design has shown that 95.5% of 1061 South Asians participants agree that the intervention increases their knowledge on cervical cancer, 95.7% report understanding of the importance of screening, and 93.8% know where to go for screening [13]. Despite the positive effects of the multimedia intervention, focus group interviews have revealed that some participants experience difficulties in scheduling and attending health services for screening because of language and cultural barriers. Further limitations on studies reporting these interventions include the lack of randomization and evaluation of the rate of screening uptake by participants. Thus, strategies that enhance the participants’ access to screening services and address methodological limitations should be developed.

Strategies such as interventions led by community health workers (CHWs) may circumvent the aforementioned limitations and reduce screening disparities [14]. CHWs are lay individuals within a community, and they are trained as participants who link the members of the community with healthcare providers to facilitate intervention [15]. The advantage of CHW involvement in health-related interventions is their strong integration into the social and religious lives of their ethnic communities. They can be trained as culturally compatible role models to ensure that their involvement in the development and delivery of an intervention ensures cultural appropriateness of the intervention, can help provide support, and can reinforce healthy behaviors of the intervention participants [16]. The components of CHW-led interventions usually involve provision of health education and services, support, and navigation, such as helping their peers find their way through health systems to ensure timely screening [16].

CHW-led interventions have successfully motivated the use of cancer preventive services and enhanced access to these services among ethnic minority women [15, 16]. CHW-led interventions also offer a more cost-effective approach to increase cancer screening uptake than other interventions [17]. A systematic review has demonstrated that CHW-led interventions are effective in increasing screening utilization among participants who are ethnically concordant with the CHWs [18]. Another recent trial involving 560 women examining the effects of a CHW-led intervention has demonstrated that the self-reported utilization rate of the Pap test among participants in the intervention arm at 6 months was 13.3 times higher than that in the control arm (95% CI = 7.9, 22.3) [19]. However, this study is limited by the use of subjective measures to assess screening uptake.

To address the limitations of previous multimedia educational interventions [13] and CHW-led interventions, we propose to develop an educational intervention by adopting an innovative approach that combines the use of multimedia and CHWs in the intervention. We will then evaluate its effects in a randomized wait-list controlled trial. This approach will potentially provide significant practical implications in addressing the needs and increasing the uptake of cervical cancer screening of South Asian women. Ultimately, this study will help reduce screening disparities, enhance the awareness of South Asian women on the importance of cancer screening on cervical cancer prevention, and reduce the healthcare cost incurred by treatment and care of cervical cancer patients.

## Theoretical framework

The two theoretical frameworks used to guide the development of this intervention are the Health Belief Model (HBM) [20] and the PRECEDE–PROCEED framework [21]. The HBM consists of six factors that determine readiness for healthy behavioral change: perceived susceptibility to the disease, perceived severity of the disease, perceived benefits, perceived barriers to recommended action, self-efficacy in taking recommended action, and cues to the action on that recommendation [20]. The HBM has been widely used in behavior-related health research, and is also recommended as a conceptual framework for the development of health behavior interventions, including those concerning cancer prevention [20].

The PRECEDE–PROCEED framework is a planning model for the development of behavioral change interventions. This framework emphasizes the needs of a target population and ensures that the intervention will be an accessible, acceptable, and effective means for working with ethnic minority groups. This framework allows the conceptualization of three main factors (predisposing, enabling, and reinforcing factors) which influence health behavior. The predisposition of factors, including knowledge, attitudes, and beliefs, influences an individual’s motivation for the target behavior. Enabling factors are those that empower an individual to act on motivation and accomplish the target behavior. Reinforcing factors promote the continuation of the particular behavior. Examples of such factors are reminders, positive reinforcement, and social support [22]. In this study, the HBM will be integrated into the PRECEDE portion of the PRECEDE–PROCEED framework to guide intervention development. These two frameworks can complement each other by focusing on health behavioral change and covering crucial factors that are likely to increase cancer screening uptake among ethnic minority women [22–24]. Figure 1 shows the theoretical framework.

**Fig. 1 Fig1:**
[figure not shown]
Theoretical framework to guide the development of the community health worker (CHW)-led intervention

## Objectives

The primary objective of this study is to evaluate the effects of a CHW-led multimedia intervention as measured by the uptake of cervical cancer screening among South Asian women immediately after and 3 months after completion of the intervention. The secondary objective is to assess the effects of such intervention on readiness to undergo screening and beliefs regarding cervical cancer screening (including perceived susceptibility to and seriousness of cancer, perceived benefits and barriers of cancer screening, and self-efficacy to undergo cancer screening) among those women.

## Hypothesis

Compared with the wait-list control arm, South Asian women in the intervention arm are expected to exhibit the following outcomes upon completion of the CHW-led multimedia intervention:higher rates of cervical screening uptake evidenced by a record/receipt of screening utilization;higher levels of readiness to undergo cervical cancer screening assessed by a question on readiness to undergo such screening; andhigher levels of perceived susceptibility to and seriousness of cervical cancer, perceived benefits of cancer screening, self-efficacy to undergo cancer screening, and lower levels in perceived barriers of cancer screening. (All items will be measured by the Cervical Cancer Screening Belief Scale.)

## Methods

### Design

This project has two phases. Phase I aims to recruit and train six CHWs who will lead the intervention in Phase II. Phase II is a cluster randomized wait-list controlled trial that aims to implement and evaluate the effects of the intervention. The rationale of using a wait-list control is to allow an untreated comparison for the intervention arm to determine whether the intervention has an effect. In addition, it allows the wait-listed participants who have never had a Pap test and have not undertaken cancer screening in the past 5 years to have the opportunity to receive future interventions.

Standard Protocol Items: Recommendations for Intervention Trials (SPIRIT) 2013 (Additional file 1) will be used to report the study. The schedule for study enrollment, intervention, and outcome assessments is shown in Fig. 2 in the form of a SPIRIT diagram.

**Fig. 2 Fig2:**
[figure not shown]
Standard Protocol Items: Recommendations for Interventional Trials (SPIRIT) figure. CHW community health worker, Pap Papanicolaou, T0 baseline (i.e., upon entry to the study after randomization but before participants receive the intervention), T1 immediate post intervention (3 months after T0, i.e., upon completion of the intervention), T2 3 months post intervention (6 months after T0, i.e., 3 months after completion of the intervention)

### Subjects

#### Subjects for Phase I: CHWs

Six CHWs (two Indians, two Nepali, and two Pakistani) will be recruited from six different community centers or ethnic minority associations in Hong Kong. These CHWs will be nominated by the persons in charge of these centers or associations involved in cancer prevention and women’s health among South Asians. A panel of research team members including three professors, one research nurse, and one research assistant with a medical background will select the most appropriate nominees. The potential CHWs should meet the following six criteria: able to demonstrate an understanding of South Asian women’s health needs and sociocultural norms; fluency in English and Urdu/Nepali/Punjabi/Hindi; willing to participate in community outreach activities and provide health information, healthcare, and social services relevant to cancer prevention; willing to complete the CHW training program and meet its requirements; and willing to serve as CHWs.

#### Subjects for Phase II: participants in the study

Prior to randomization, a trained research assistant (RA1) fluent in English and Urdu/Nepali/Punjabi/Hindi will approach potential subjects while they are attending various activities organized by the six participating community centers or ethnic minority associations. After an introductory presentation, women interested in participating in the study will be screened for eligibility. Inclusion criteria include: self-identified as South Asian (Pakistani, Indian, or Nepali); aged 25 years or older who have previously had sex; never had a Pap test or has not undertaken cancer screening in the past 5 years; have not been previously diagnosed with cancer; have not attended any intervention or education program related to cervical cancer screening in the previous year; and able to communicate in English, Urdu, Nepali, Punjabi, or Hindi and read English, Urdu, Nepali, or Punjabi.

### Sample size

The calculation of sample size is based on our previous survey on Hong Kong South Asians indicating that only 37% of them ever had a Pap test [7]. We anticipated that our intervention can increase the rate to at least 60%. By using power analysis software, PASS 14.0 (NCSS, Kaysville, UT, USA), it is estimated that 72 participants per arm will enable a two-parallel arm design with 80% power to detect a rate difference of at least 23% at a two-sided 5% level of significance, assuming the rate in the control is not greater than 37%. To allow for an attrition rate up to 15%, 85 participants in each arm will be needed. Furthermore, to account for potential reduction in statistical efficiency due to randomization by ethnic minority association (cluster) instead of individual participant, a variance inflation factor, called the design effect, is needed to impose on the sample size estimated [25]. The design effect is given by the equation: Design effect = 1 + (*m* – 1) × ICC, where *m* is the average cluster size and ICC is the intracluster correlation coefficient of the underlying outcome. A synthesis study revealed that the ICC tends to be small in primary care research, with a median of 0.005 and an interquartile range of 0.000–0.021 [26]. Allowing for an ICC of 0.021 in our proposed trial, at least 68 participants need to be recruited from each of the six ethnic minority associations—the number of participants in each cluster, *m*, is determined from the equation: number of participants = 2 × 85 × [1 + (*m* – 1) × 0.021] = 6 × *m*.

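### The 80% power claim does not hold at the protocol's own ICC of 0.021 with three clusters per arm, and the planned permutation test cannot reach a two-sided 5% level

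*Protocol article*

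**What the plan says.** The Sample size section of the protocol article builds the number in three steps.

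- **Individual-level size.** The control rate enters as "assuming the rate in the control is not greater than 37" per cent, and for the intervention arm: "We anticipated that our intervention can increase the rate to at least 60" per cent. The test is "at a two-sided 5% level of significance". The result is that "72 participants per arm will enable a two-parallel arm design with 80% power to detect a rate difference of at least 23" percentage points.
- **Attrition.** "To allow for an attrition rate up to 15%, 85 participants in each arm will be needed".
- **Clustering.** "Allowing for an ICC of 0.021 in our proposed trial", the design effect 1 + (m − 1) × ICC is applied, and "at least 68 participants need to be recruited from each of the six ethnic minority associations". The Abstract gives the total: "A total of 408 South Asian women from Pakistan, India or Nepal will be recruited from six ethnic minority associations". The associations are randomised three to each arm.

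The section cites a median ICC of 0.005 and an interquartile range of 0.000 to 0.021, so the design value is the upper quartile.

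The Statistical analysis section compares uptake at T2 by a permutation test. Differences are computed for every possible arm assignment of the six associations, and the 2.5th and 97.5th percentiles of those differences are the critical values. The changes in readiness are tested in the same way. The overall level is two-sided 0.05.

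**The concern.** A design effect restores the right variance for a clustered comparison. It does not change the reference distribution, and the calculation it multiplies here uses normal critical values. That does little harm with many clusters. With three per arm, a test that estimates between-cluster variation from the six association results has only 4 degrees of freedom, and its critical value is 2.776 rather than 1.96. The planned permutation test avoids the t distribution but meets a harder limit, because the number of possible assignments sets a floor under its p-value.

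A non-significant result would be read against a stated 80% chance of detecting 23 points that the design does not have. In addition, depending on how the percentile rule is programmed, the primary test either can never be significant or runs at a level above the stated 5%.

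**Working it through.** **Inputs** (Sample size section): p1 = 0.37, p2 = 0.60, two-sided α = 0.05, attrition 15%, ICC 0.021, six clusters of 68, three per arm.

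**1. The plan's own figures**
- The pooled two-proportion formula gives 73 per arm. At 72 per arm, power is 79.5%. The stated 72 at 80% reproduces.
- 72 / 0.85 = 84.7, rounded up to 85.
- Solving 170 × [1 + (m − 1) × 0.021] = 6m gives m = 170 × 0.979 / (6 − 3.57) = 68.49. With 84.7 unrounded in place of 85, m = 67.9. The stated 68 is within rounding.
- Check: 3 × 68 = 204 per arm; design effect 1 + 67 × 0.021 = 2.407; 204 × 0.85 / 2.407 = 72.0 effective per arm.

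**2. A valid cluster-level test with six clusters**
- Analysed per cluster: 68 × 0.85 = 57.8.
- Design effect: 1 + 56.8 × 0.021 = 2.193.
- SE = √[(0.37 × 0.63 + 0.60 × 0.40) × 2.193 / (3 × 57.8)] = √[0.4731 × 2.193 / 173.4] = 0.0773.
- Non-centrality: 0.23 / 0.0773 = 2.97.
- Non-central t, 4 df, critical value 2.776: power **61.2%**. A beta-binomial simulation of this t test (58 per cluster, 40,000 runs) gives 61.0%, with a rejection rate of 5.0% under no effect.
- The normal distribution with the same SE gives 84.5%, so the gap comes from the reference distribution and not from the variance.

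| Analysed per cluster | ICC | Power, 4-df t test |
|---|---|---|
| 57.8 | 0 | 90% |
| 57.8 | 0.005 | 82% |
| 57.8 | 0.021 | 61% |
| 68 (no attrition) | 0.021 | 64% |

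At ICC 0.021 and 57.8 analysed, 80% power needs a non-centrality of about 3.76. That is reached at about 65.6% versus 37%, a difference of about 29 points.

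**3. The test the plan names**
- Number of assignments: C(6,3) = 20.
- The most extreme split and its mirror image are both counted in a two-sided test, so the smallest p-value is 2/20 = 0.10. A strict two-sided 5% test never rejects, and its power is 0% whatever the effect.
- If the percentiles are linearly interpolated, the 97.5th falls between the largest and second-largest of the 20 differences. An observed difference that is the largest then exceeds it. In simulation (58 per cluster, ICC 0.021) this rule has about 72% power, and it rejects in about 8% of trials with no effect. Without ties the rate would be 10%; tied differences lower it.

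**The case against.** The strongest objection is that no t test of uptake is planned, so 4 degrees of freedom and a power of 61% do not describe this trial. That stands in part. A reader might infer that the trial has 61% power, and the documents do not support it, because the named primary test is a permutation test. The 61% is what a conventional valid 5% analysis of this design would have. It shows that the 80% is not delivered but is not the power of the planned analysis, which at a strict 5% level is zero. Entering 61% in the Sample size section while leaving Statistical analysis unchanged would add a second false figure.

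Three other stronger readings are also tempting, and none holds.

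- **That the 72 per arm is miscalculated.** It reproduces. The fault is in carrying it to six clusters.
- **That the cluster size should be 69 (414 women).** The difference arises only from re-using the rounded 85. The unrounded figure gives 67.9, and the text asks for at least 68.
- **That 80% is out of reach at any ICC.** At the cited median of 0.005 the 4-df t test has 82%, and it reaches 80% up to an ICC of about 0.0065. The protocol was also cautious in choosing the upper quartile. But it chose 0.021 as the design value and attached its 80% to that value, and there the claim fails.

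**Conclusion.** The point holds conditionally. At the protocol's ICC of 0.021, the stated 80% power for 37% versus 60% is not delivered, because no allowance is made for three clusters per arm. A 4-df cluster-level t test has about 61% power (64% with no attrition) and detects about 29 points rather than 23 at 80% power. The planned permutation test either has no power at a true two-sided 5% level or, with interpolated cut-offs, has about 72% at a true level of about 8%. Neither gives 80% at 5%.

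These figures assume equal cluster sizes, 15% loss in every cluster, the same ICC in both arms and unpooled variances; pooling gives 59% instead of 61%. The floor of 0.10 on the permutation p-value needs none of these assumptions. It applies equally to the readiness comparisons tested by the same rule.

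**What to change.** Keep the six associations and change two sections together.

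- **Statistical analysis.** Name a primary analysis that can reach two-sided 5% with three clusters against three, for example a t test on the six association-level proportions with 4 degrees of freedom. Alternatively, keep the permutation test, say exactly how the percentile cut-offs are computed and whether a tie counts as significant, and state the level it really has.
- **Sample size.** Replace the 80% claim with the power of whichever analysis is named. For the 4-df t test at ICC 0.021 and 15% attrition, that is about 61% for 23 points, or about 29 points at 80% power. Giving the 82% at the cited median ICC of 0.005 beside it shows how far the answer depends on the ICC.

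The cost is a short revision of both sections and a less favourable stated power. Naming a t test also means relying on approximate normality of six cluster proportions, which six values cannot verify. The 68 per association and the total of 408 can stay.
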